### **10.2 Randomization**

We will include 10 patients in each of the three study arms and 10 in the control arm. By open label randomization TB patients meeting the inclusion criteria will be included in a 2:2:1 fashion in the arms #1, #2 and #3. When the last patient have reached study day 98 (end of etoricoxib treatment), arms #4 and rest of controls arm #3 will be recruited in a 2:1 fashion if safety issue are satisfactory in arms #1, #2 and #3.

### **10.3 Population for Analysis**

A table will be provided with the following information:

- number of subjects, both screened and enrolled, included in the study
- number of subjects included in the immunogenicity analysis

- number of subjects included in the safety analysis
- number of subjects withdrawn from the study and the reason for withdrawal

The following populations will be considered for the analyses:

- Intention to treat (ITT) population: All randomized participants, regardless of protocol adherence.
- Per-protocol population (PP): Includes all subjects who have received at least one dose of etoricoxib and/or H56:IC31.
- Safety population: Includes all subjects who have received at least one dose of etoricoxib and/or H56:IC31. Subjects who withdraw from the study will be included in the safety analysis. A list of withdrawn subjects, preferably with the reasons for withdrawal, will be made.

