## Statistical methods – detailed description

The primary outcomes on safety were performed on the safety analysis set (SAS) (described in section statistical methods in article). The secondary outcomes of immunogenicity were assessed on the full analysis set (FAS). To acknowledge the possible impact of poor compliance to allocated treatment on immunogenicity, we calculated compliance for each group based on a priori definitions. For all arms, a participant was considered compliant if no corticosteroids/additional NSAIDs during the last seven days prior to sampling were taken. In addition, if allocated to etoricoxib,  $\geq 80\%$  of prescribed daily doses had to be taken during 1) the day 0-140 interval, and 2) the last 7 days prior to sampling. If allocated to H56:IC31-vaccine,  $\geq 1$  H56:IC31-vaccine were administered. The number (and percentage) of patients that were compliant with major treatment are presented but no per protocol analyses were performed.

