| TB disease progression                                           | 1 (25%)                | 0 (0%)               | 0 (0%)               | 0 (0%)                               |
| Autoimmune disease or immunosuppressive therapy during follow-up | 0 (0%)                 | 0 (0%)               | 1 (33%)              | 0 (0%)                               |
| Moved abroad                                                     | 1 (25%)                | 1 (50%)              | 0 (0%)               | 1 (25%)                              |

\*Safety analysis set defined as patients that received at least one dose of etoricoxib and/or one dose of H56:IC31

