**Time-line (anti-TB chemotherapy, day 0-182)**

### Supplementary Figure 9

The safety profile of COX2i or H56:IC31 has not yet been determined in a population undergoing treatment for pulmonary TB. Therefore, we will enrol participants in two groups separated by a safety review. Group A includes volunteers for arm #1, arm #2 and arm #3 (2:2:1 randomization). First at the completion of Study Day 98 for all group A participants, the “clinical investigational group” (sponsor, PI, collaborators including representative from the H56:IC31 vaccine manufacturer) will meet and evaluate the cumulative safety data to determine if the observed safety profile meets the criteria to proceed to inclusion of volunteers for group B; arm #4 and remaining Arm #3 controls (2:1 randomization).

Arm #1 (n=10): etoricoxib treatment started at day 0 and given for 20 weeks (day 0-140) followed by 6 weeks (or according to clinical evaluation) of standard anti-TB chemotherapy alone (day 0-182) and follow-up control at day 210 and day 238.

Arm #2 (n=10): given anti-TB chemotherapy alone (day 0-182) (or according to clinical evaluation) and follow-up control at day 210 and day 238. TB vaccine H56:IC31 will be injected at day 84 and day 140.

Arm #3 (controls, n=10): given anti-TB chemotherapy alone (day 0-182) (or according to clinical evaluation) and follow-up control at day 210 and day 238.

Arm #4 (n=10): etoricoxib treatment started at day 0 and given for 20 weeks (day 0-140) followed by 6 weeks (or according to clinical evaluation) of standard anti-TB chemotherapy alone and follow-up control at day 210 and day 238. TB vaccine H56:IC31 will be injected at day 84 and day 140.

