## **10.4 Statistical Analysis**

Groups will be compared with non-parametrical statistical methods throughout with two-ways tests using p-values equal to or below 0.05 as significant. No adjustments due to multiple comparisons will be performed.

Deviation from the original statistical plan will be described and justified in the Clinical Study Report. The investigators can make the decision regarding individual values belonging to a subject to be excluded from the statistical evaluations, but only when a protocol violation is considered to weaken any of the scientific aspects of the study. Missing data will not be substituted by estimated values, but will be treated as missing data by the method used.

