#### **10.4.6 Immunogenicity and Other Immunology Analyses**

All immunogenicity analyses will be based on subjects who has received etoricoxib until the sample time-point in question and/or received at least one dose of study vaccine H56:IC31. Immunogenicity will be summarized for all time points as collected and as available. No imputation for missing data will be performed. Data will be transformed as appropriate prior to analysis.

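### Sections 10.3 and 10.4.6 define the safety, per-protocol and immunogenicity sets by receipt of study product, so read literally they exclude every control, and the ITT set that contains them is tied to no analysis

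*Protocol*

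**What the plan says.** Section 10.3 lists three populations.

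- ITT: "Intention to treat (ITT) population: All randomized participants, regardless of protocol adherence".
- Per-protocol: "Per-protocol population (PP): Includes all subjects who have received at least one dose of etoricoxib and/or H56:IC31".
- Safety: "Safety population: Includes all subjects who have received at least one dose of etoricoxib and/or H56:IC31".

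The last two are the same set. Section 10.4.6 adds a fourth basis: "All immunogenicity analyses will be based on subjects who has received etoricoxib until the sample time-point in question and/or received at least one dose" of the vaccine.

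The control arm is described in section 3: "Arm #3 (controls, n=10): given anti-TB chemotherapy alone (day 0-182"). Section 5.1.3 rules out placebo for either product. The arm table in section 3 (Supplementary Table 12) nevertheless gives arm 3 both safety and immunogenicity as endpoints, in the role of control. Section 10.4 says that groups will be compared, and section 10.4.6.1 promises summaries for all study groups.

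The supplementary material in the same document goes two ways. The footnotes to Supplementary Table 8 keep the receipt rule: "Safety analysis set defined as patients that received at least one dose of etoricoxib and/or one dose of H56:IC31". For immunogenicity, the detailed statistical methods say: "The secondary outcomes of immunogenicity were assessed on the full analysis set (FAS"). Supplementary Table 8 defines that full analysis set as randomised patients with a valid immunogenicity measurement, and it contains 10 controls. Supplementary Tables 3 and 4 specify contrasts that use controls: groups 1+4 against 2+3, and group 2 against 3.

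**The concern.** Safety and tolerability is the primary objective, and arm 3 is there to show what happens on chemotherapy alone. A safety set that requires a study product has no control denominator, and the same holds for an immunogenicity set built that way. Anyone applying the definitions as printed would get different patients from those in the published tables.

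The receipt rule also depends on what happens after randomisation. An arm 1 patient who stops etoricoxib loses all later samples, and stopping is often linked to intolerance. An arm 2 patient is admitted only if vaccinated, and section 4.5 allows vaccination only after clinical improvement, plus negative sputum in pulmonary TB. The groups then stop being the randomised groups, and an immune-response contrast can reflect who tolerated the drug or improved on chemotherapy. The safety rule has a related gap: an arm 2 patient who leaves before day 84 never enters the safety set.

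**Working it through.** **1. Inputs.** Supplementary Table 8 gives the safety set as 13 (etoricoxib), 12 (H56:IC31), 12 (controls) and 10 (combination). Its adherence tables show a lowest tablet proportion of 73.5% in arm 1 and 92.8% in arm 4, so every patient there took etoricoxib. In arm 2, 11 of 12 had the first vaccination and 10 of 12 the second.

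**2. The tabulated figure.** 13 + 12 + 12 + 10 = 47. The arm columns add up to the stated total.

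**3. The printed definition applied to those patients.** Arm 1: 13. Arm 2: 11 with a first dose. Arm 3: 0. Arm 4: 10.

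13 + 11 + 0 + 10 = 34.

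Section 6.4.1 lets a patient who missed the first injection receive the second, and the adherence table does not exclude this for the one arm 2 patient without a first dose. The upper limit is therefore 13 + 12 + 0 + 10 = 35. The definition does not reproduce 47 either way.

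**4. The gap.** 47 − 34 = 13 patients (13/47 = 27.7%), or 47 − 35 = 12 patients (12/47 = 25.5%). These are the 12 controls and possibly one unvaccinated arm 2 patient.

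**5. The planned trial.** With 10 per arm, the safety and per-protocol sets hold at most 10 + 10 + 0 + 10 = 30 of 40 patients and 0 of 10 controls. The ITT set holds all 40.

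**6. Immunogenicity.** The full analysis set is 10 + 12 + 10 + 8 = 40. In it, 11 of 12 arm 2 patients and 8 of 8 arm 4 patients had a first vaccination. The table counts patients before any loss of arm 1 samples after stopping etoricoxib.

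| Contrast | Full analysis set | Section 10.4.6 read literally |
|---|---|---|
| Groups 1+4 vs 2+3, day 0–84 | 18 vs 22 | at most 18 vs 11 (at most 12) |
| Group 2 vs 3, day 84–154 | 12 vs 10 | 11 (at most 12) vs 0 |
| Group 4 vs 2, day 84–154 | 8 vs 12 | 8 vs 11 (at most 12) |

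The first row assumes that a later vaccination qualifies a patient's earlier samples. Section 10.4.6 does not say so. If the dose had to precede the sample, arm 2 would also drop out of the day 0–84 contrast and leave it with no comparator.

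**7. Does stopping etoricoxib occur?** The summary in Supplementary Table 9 reports adverse events leading to drug discontinuation by day 84 in 2 of 13 arm 1 and 4 of 10 arm 4 patients, with 2 and 7 events. The listing by preferred term gives 1 + 1 + 1 + 1 + 3 = 7 events in arm 1 and 1 + 1 + 1 = 3 in arm 4. The two disagree on the split, so I use them only to show that stopping did happen.

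**The case against.** The strongest reply is that controls were never lost. Section 10.3 defines an ITT set that includes them, section 10.4 provides for group comparison, the supplement writes out control contrasts on a full analysis set with 10 controls, and every adverse-event summary has a control column. A reader might infer that the plan contains no comparison with standard therapy, or that the reported results lack controls. The documents support neither. What stands is that section 10 attaches no analysis to ITT and that three working definitions leave arm 3 out.

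Other tempting readings also go too far:

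- **All three immunogenicity contrasts need controls.** They do not. Group 4 against group 2 uses none.
- **The on-drug rule falls on the etoricoxib arms alone.** It does not. The same sentence selects arm 2 on vaccination. Because the two conditions are joined by and/or, a vaccinated arm 4 patient who stopped etoricoxib stays in. The on-drug condition therefore acts mainly on arm 1, and sample by sample.
- **Investigators may delete values at will.** Section 10.4 says "The investigators can make the decision regarding individual values belonging to a subject to be excluded from the statistical evaluations", but goes on to limit this to protocol violations judged to weaken the science. It sets no timing or masking for the decision in an open-label trial, which is a lesser matter.

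It can also be said that the supplement reports no per-protocol analyses, so the empty per-protocol definition changes no result; that safety was descriptive without testing; and that a final SAP exists which is not shown. These points reduce the consequences. They do not excuse the text: the protocol fixes a definition that does not fit its design, and the supplement, written after SAP version 1.0, prints the same safety definition above a control column.

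**Conclusion.** The point holds as a contradiction in the stated analysis sets. The safety, per-protocol and immunogenicity definitions exclude all controls, against the purpose of arm 3 and the document's own tables and contrasts. For the safety set the size is 34 to 35 patients by definition against 47 tabulated, with 0 against 12 controls. For group 2 against group 3 the comparator would be 0 rather than 10. Section 10.4.6 also replaces randomised groups with groups selected on drug continuation in arm 1 and on vaccination in arm 2. The direction and size of any resulting bias cannot be derived from the documents.

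The counts rest on the adherence figures in Supplementary Table 8 and on a literal reading of the definitions. The range 34 to 35 covers the one patient whose vaccination status is not fully determined. The safety definition matters most because it serves the primary objective. The per-protocol definition is secondary.

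**What to change.** - **Section 10.3, safety set:** all randomised patients who started follow-up at day 0, controls included, tabulated by study arm as the supplement's methods already do. This reproduces 47 if the tabulated patients are all who were randomised and started. The documents do not give the number randomised, so that needs confirming. Grouping by product received instead would, on first-dose counts, turn 13/12/12/10 into 15/11/13/8 and pool patients from the two sequential enrolment groups.
- **Supplementary Table 8:** correct the safety-set footnotes to match.
- **Section 10.4.6:** replace the receipt rule with the full analysis set, meaning randomised patients with a valid immunogenicity measurement, analysed in the allocated arm whether or not they stopped etoricoxib or missed a vaccination. State in section 10 which analyses use this set and which, if any, use ITT.
- **Per-protocol set, if kept:** define it by the compliance rules in the supplement's statistical methods: no corticosteroids or additional NSAIDs in the seven days before sampling, the 80% threshold for etoricoxib, and at least one vaccination where allocated.

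The cost is wording in sections 10.3 and 10.4.6 and the table footnotes. No new data are needed.

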## **10.4 Statistical Analysis**

Groups will be compared with non-parametrical statistical methods throughout with two-ways tests using p-values equal to or below 0.05 as significant. No adjustments due to multiple comparisons will be performed.

Deviation from the original statistical plan will be described and justified in the Clinical Study Report. The investigators can make the decision regarding individual values belonging to a subject to be excluded from the statistical evaluations, but only when a protocol violation is considered to weaken any of the scientific aspects of the study. Missing data will not be substituted by estimated values, but will be treated as missing data by the method used.

### **10.4.1 Safety analysis**

The number and percentages of patients with at least one AE will be tabulated. Occurrence of particular AEs and their severity and relationship to study drug will be summarized.

### **10.4.2 Vital Signs**

Categorical data will be summarized by treatment and as a total using count and percentages of patients. Continuous data will be summarized by treatment and as a total using medians, quartiles and ranges.

### **10.4.3 Physical Examinations**

Categorical data will be summarized by treatment and as a total using count and percentages of patients. Continuous data will be summarized by treatment and as a total using median, quartiles and ranges.

### **10.4.4 Clinical Laboratory Measurements**

Categorical data will be summarized by treatment and as a total using count and percentages of patients. Continuous data will be summarized by treatment and as a total using median, quartiles and ranges.

### **10.4.5 Pharmacokinetics**

The AUC and Cmax of etoricoxib at steady state after 7 days of treatment will be analyzed and statistics performed as previously described (32).

#### **10.4.6 Immunogenicity and Other Immunology Analyses**

All immunogenicity analyses will be based on subjects who has received etoricoxib until the sample time-point in question and/or received at least one dose of study vaccine H56:IC31. Immunogenicity will be summarized for all time points as collected and as available. No imputation for missing data will be performed. Data will be transformed as appropriate prior to analysis.

##### **10.4.6.1 Primary Immunogenicity endpoints**

The primary variables of interest for assessment of immune response to vaccine will be the percentage of CD4+ and CD8+ T cells that produce any of selected cytokines. The immunogenicity of H56:IC31 in this study will be evaluated by PBMC ICS, T-cell proliferation and IL-2/IFN- $\gamma$  ELISPOT. Due to the exploratory nature of immunogenicity endpoints, the primary evaluation will be based on descriptive summaries and no formal hypothesis testing will be performed.

##### **PBMC/whole blood ICS Assay**

Assessment of immune response by PBMC or whole blood ICS will be based on the percentage of cytokine producing CD4+ and CD8+ T cells in response to stimulation with H56 protein antigen and antigenic peptide pools (Ag85B, ESAT-6, Rv2660c, CFP-10). ICS parameters will include cytokines such as IFN- $\gamma$ , IL-2 and TNF- $\alpha$ , and may include other cytokines to identify T cells of specific functionality. Additional cell surface markers, cytokines, or functional markers may also be analysed. Median control-subtracted cytokine responses and associated 95% confidence intervals (CIs) or other descriptive statistics as appropriate will be used to summarize the percentage of antigen-specific CD4 and CD8 T cell responses by all study group and treatment assignment at all available time points. Summaries of T cell responses will be presented by T cell type (CD4 and CD8), by stimulation antigen(s), and by cytokine profile. Summaries will include immune responses at all available pre- and post- etoricoxib and pre- and post-vaccination time points. Exploratory assessment of antigen specific CD4+ and CD8+ T cell responses in relation to the magnitude of QFT positivity pre and post-study may also be performed.

##### **T cell proliferation**

Assessment of T cell proliferation will be based on the percentage of CD4+ and CD8+ T cells expressing the proliferation marker cfse in response to stimulation with H56 protein antigen and antigenic peptide pools (Ag85B, ESAT-6, Rv2660c, CFP-10). Fraction of cell subsets and responses and associated 95% confidence intervals (CIs) or other descriptive statistics as appropriate will be used to summarize the percentage of antigen-specific CD4+ and CD8+ T cell responses by all study group and treatment assignment at all available time points. Summaries of T cell responses will be presented by T cell type (CD4 and CD8) and by stimulation antigen(s) at all available pre- and post- etoricoxib and pre- and post-vaccination time-points.

##### **ELISPOT**

Assessment of immune response by ELISPOT will be based on the number of IL-2/IFN- $\gamma$  spot-forming units (SFU) per  $10^6$  PBMC in response to stimulation with H56 antigen and antigenic peptide pools (Ag85B, ESAT-6, Rv2660c, CFP-10). Geometric mean and associated 95% CIs will be used to summarize the number of IL-2/IFN- $\gamma$  SFU per  $10^6$  PBMC by study group and treatment assignment at all available time points. Summaries of the number of IL-2/IFN- $\gamma$  SFU per  $10^6$  PBMC will be presented by stimulation antigen(s) and will include immune response at all available pre- and post- etoricoxib and pre- and post-vaccination time-points.

## **QuantiFERON-TB Gold Test**

Results for the QuantiFERON-TB Gold test at baseline day 0 and day 182 will be summarized using subject count (percentage) summaries and descriptive statistics.

### **10.4.6.2 Exploratory Assays**

#### **dcRT-MLPA (RNA Analysis)**

As an exploratory endpoint for examining RNA gene expression signatures, RNA expression will be performed. RNA will be isolated from whole blood. Signatures of gene expression changes after vaccination may be determined using computational systems biology tools.

#### **Antibody IgG ELISA**

Geometric mean titers for antibody ELISA to Ag85B, ESAT-6, and Rv2660c and associated 95% CIs will be summarized at all pre- and post-vaccination time-points.

#### **PBMC flow cytometry Assay**

Assessment of immune phenotyping and responses by PBMC will be based on the percentage of CD4+ and CD8+ T cells and monocytes expressing various markers of activation, regulation, maturity and COX-2 *ex vivo* and in response to stimulation with H56 protein antigen and antigenic peptide pools (Ag85B, ESAT-6, Rv2660c) and eventually with peptides representing non-vaccine *Mtb*-derived antigens (TB10.4, CFP10, PPD). Fraction of cell subsets and responses and associated 95% confidence intervals (CIs) or other descriptive statistics as appropriate will be used to summarize the percentage of antigen-specific CD4+ and CD8+ T cell responses by all study group and treatment assignment at all available time points. Summaries of T cell responses will be presented by T cell type (CD4 and CD8), by stimulation antigen(s), and by marker profile at all available pre- and post-atoricoxib and pre-and post-vaccination time-points.

## **11 STUDY MANAGEMENT**

### **11.1 Investigator Delegation Procedure**

The principal investigator is responsible for making and updating a “delegation of tasks” listing all the involved co-workers and their role in the project. He will ensure that appropriate training relevant to the study is given to all of these staff, and that any new information of relevance to the performance of this study is forwarded to the staff involved.

### **11.2 Investigator’s Responsibilities**

The investigator(s) is responsible for performing the study in accordance with this protocol and the ICH guidelines on GCP, and for collecting, recording, and reporting the data accurately and properly. Agreement of the investigator to conduct and administer this study in accordance with the protocol will be documented in a separate study agreement.

The investigator has the overall responsibility for the conduct and administration of the study at the centre, and for contacts with study centre management, the EC and with local authorities.

The investigator is responsible for giving information about the study to all staff members involved in the study or in any element of subject management, both before starting the practical performance of the study and during the course of the study (e.g., when new staff become involved).

The investigator(s) is responsible for ensuring the privacy, health, and welfare of the subjects during and after the study. The investigator must be familiar with the background and requirements of the study and with the properties of the study drugs as described in the package insert.

Authorised personnel of the Regulatory Authority inspector(s) or their agents will be given direct access to source data and documentation (e.g., medical charts/records, laboratory results, printouts, etc.) for source data verification, provided that subject confidentiality is maintained.

